
### 2.7 Sample Size Estimation

The main objective of this study is to provide preliminary data on the effect of PRP in reducing musculoskeletal pain compared to placebo plaster. We conservatively anticipate lost to follow up to be at most 10% by day 7. To ensure adequate power to compare arms on our secondary symptom endpoints, we will enroll 66 patients to obtain at least 60 patients evaluable for these secondary symptom endpoints. Our sample size will provide sufficient statistical power to detect clinically relevant effect sizes for our primary pain outcome between PRP vs. placebo plaster (primary objective). We present our power considerations for an ANCOVA regression model (e.g., predicting Day 7 pain score controlling for baseline pain score), which we will apply to our primary pain endpoint as well as to the secondary symptom endpoints. However, our analysis method for our primary endpoint (linear mixed model) will be able to detect a slightly smaller effect size than presented here. For our sample size/power considerations, we calculated the smallest standardized effect size we will be able to detect with 0.80 power, given a sample size of 60. With 30 participants in each of the two arms, we will have power of 0.80 to detect an effect size of 0.74 (standardized mean difference, Cohen’s d) between the two arms at Day 7, using a two-sided test with alpha of 0.05 in a regression model controlling for baseline score. This 0.74 effect size is considered a moderate-to-large effect size by convention. Given the standard deviation of the BPI pain severity subscale typically ranges between 2 and 3, this effect size translates to a mean difference between the arms of around 1.5 to 2.25 points on the 0–10 BPI scale. A 1-point difference in BPI severity is clinically important (Dworkin et al., 2008). In addition, this criteria is also used in a recent high-impact publication comparing opioid vs. nonopioid medication for chronic low back pain (Krebs et al., 2018). Even if we find no statistically significant difference between the arms on the primary endpoint, we will estimate and report the observed effect size and 95% confidence interval to assist in planning potential larger trials.

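### The claim of sufficient power for clinically relevant effects is not supported at the 1-point difference that the protocol itself calls clinically important

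*Protocol article*

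**What the plan says.** Everything relevant to the power claim is in section 2.7 (Sample Size Estimation) of the protocol article. It makes a general claim: "Our sample size will provide sufficient statistical power to detect clinically relevant effect sizes for our primary pain outcome". The calculation behind it is: "With 30 participants in each of the two arms, we will have power of 0.80 to detect an effect size of 0.74", "using a two-sided test with alpha of 0.05 in a regression model controlling for baseline score". The conversion to scale points rests on the statement that "the standard deviation of the BPI pain severity subscale typically ranges between 2 and 3", so that "this effect size translates to a mean difference between the arms of around 1.5 to 2.25 points". The next sentence gives the clinical benchmark: "A 1-point difference in BPI severity is clinically important". On numbers, "we will enroll 66 patients to obtain at least 60 patients evaluable".

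Three further statements bear on the point. Section 2.7 says that the main objective is preliminary data. It says that the planned linear mixed model will detect an effect slightly below the one shown, without a figure. It also promises the observed effect size and 95% confidence interval even if the primary comparison is not significant. Section 2.8.2 defines the primary test as the treatment coefficient in a mixed model of post-baseline BPI severity through Day 7, adjusted for baseline severity, assessment time and baseline opioid use.

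**The concern.** The only benchmark that the paragraph offers for a clinically relevant effect is 1 point, and the difference detectable with 80% power is 1.5 to 2.25 times as large. Placed directly after the detectable difference, the benchmark reads as support for the power claim. In fact it marks the size of effect for which the paragraph does not show adequate power.

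What is at stake is how a non-significant result would be read. A reader who has been told that the trial was sufficiently powered for clinically relevant effects may take such a result as evidence against any benefit worth having, although a 1-point benefit may still be compatible with the data.

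**Working it through.** **Inputs from section 2.7.** 30 evaluable patients per arm; two-sided alpha 0.05; target power 0.80; d = 0.74; SD of BPI severity 2 to 3; clinically important difference 1 point. The document gives no correlation between baseline and follow-up and none between daily scores. Every correlation below is my assumption.

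**Step 1: the protocol's own figure.** For a two-sample t test with n per arm, the noncentrality is d × √(n/2). With d = 0.74 and n = 30 it is 0.74 × √15 = 2.87. On 58 degrees of freedom the critical value is 2.00, and the noncentral t distribution gives power 0.805. The smallest d with power 0.80 is 0.736. The stated 0.74 is therefore correct, and it equals the plain two-sample value: although described as a model controlling for baseline, it takes no credit for the variance that baseline explains.

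In points, 0.74 × 2 = 1.48 and 0.74 × 3 = 2.22. The stated 1.5 and 2.25 correspond to d rounded to 0.75.

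**Step 2: power for 1 point on the same basis.** Here d = 1/SD.

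| SD | d | Power for 1 point |
|---|---|---|
| 2 | 0.50 | 0.48 |
| 2.5 | 0.40 | 0.33 |
| 3 | 0.33 | 0.25 |

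**Step 3: credit for baseline adjustment at Day 7 (assumed r).** The residual SD is SD × √(1 − r²), on 57 degrees of freedom.

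| Baseline correlation r | Power, SD 2 | Power, SD 3 |
|---|---|---|
| 0.3 | 0.51 | 0.27 |
| 0.5 | 0.59 | 0.31 |
| 0.7 | 0.76 | 0.43 |
| 0.8 | 0.89 | 0.56 |

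Power of 0.80 for 1 point needs r of about 0.73 at SD 2 and about 0.89 at SD 3.

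**Step 4: the planned Day 2–7 mixed model (assumed correlations).** I approximate the treatment coefficient by a baseline-adjusted comparison of the mean of six daily scores. With equal correlation ρ between days and correlation r with baseline, the residual variance is SD² × [(1 + 5ρ)/6 − r²].

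| Assumption | Bracketed term | Power, SD 2 | Power, SD 3 |
|---|---|---|---|
| r = 0.4, ρ = 0.9 | 0.757 | 0.59 | 0.31 |
| r = 0.5, ρ = 0.8 | 0.583 | 0.70 | 0.38 |
| r = 0.6, ρ = 0.7 | 0.390 | 0.86 | 0.53 |
| r = ρ = 0.5 | 0.333 | 0.91 | 0.59 |
| r = ρ = 0.8 | 0.193 | 0.99 | 0.82 |

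The first three rows take the baseline score to be less closely related to the daily scores than these are to each other. The last two take one common correlation throughout. Across both sets, power for 1 point runs from 0.59 to 0.99 at SD 2 and from 0.31 to 0.82 at SD 3.

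**Step 5: precision.** At an assumed r = 0.5, the half-width of the 95% confidence interval for the Day 7 difference is 2.00 × SD × √0.75 × √(2/30). That is 0.90 points at SD 2 and 1.34 points at SD 3. With a point estimate of zero, the interval would just exclude a 1-point benefit at SD 2 and would include it at SD 3.

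**The case against.** The strongest reply is that the sentence is not literally false. It speaks of relevant effect sizes in the plural and never names 1 point as the design target. If 1 point matters to patients, so do 1.5 and 2.25 points, and for those the design has 80% power. This stands. The fault is that the sentence carries no qualification and sits beside a threshold that it does not cover.

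A second reply is that 25% to 48% is not the power of the primary test. That also stands: it is an unadjusted basis, and the mixed model may reach 80% for 1 point at SD 2 under plausible correlations. But the protocol itself credits that model with only a slight gain and gives nothing from which to compute it.

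Third, the trial is described as preliminary, the detectable difference is disclosed, and an effect size with its interval will be reported whatever the result. This reduces the harm, though it does not withdraw the claim.

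Three stronger readings are tempting, and the document does not support them:

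- **A calculation error.** A reader might infer one, but every stated figure reproduces.
- **A true 1-point benefit would probably be missed.** With baseline adjustment this fails at SD 2, where every assumed correlation above gives power above one half.
- **A non-significant result would end development of the plaster.** Nothing in the document says so. It says that the estimate and interval will help to plan larger trials.

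**Conclusion.** The point holds as an unsupported power claim. What section 2.7 demonstrates is 80% power for about 1.5 to 2.25 points, not for the 1 point that it calls clinically important. On its stated basis, power for 1 point is 48% at SD 2 and 25% at SD 3; these are lower bounds, because baseline adjustment and repeated daily scores are ignored. Under the assumed correlations the mixed model reaches 80% for 1 point in part of the range at SD 2, and at SD 3 only towards the top of the more favourable set. So 80% at 1 point is not shown across the SD range that the protocol adopts. The mixed-model figures rest on equal correlation between days, complete data in 30 patients per arm, and correlations that the document does not give. Severity: should be fixed. The design, the primary analysis and the sample size are unaffected.

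**What to change.** 1. Replace the general claim in section 2.7 with what the calculation shows: 80% power for a between-arm difference of about 1.5 to 2.25 points at SD 2 to 3.
2. State the power for a 1-point difference under the Day 2–7 mixed model, with the assumed baseline and between-day correlations, at both ends of the SD range. If 25% to 48% is quoted, label it as the unadjusted lower bound, not as the power of the primary test.
3. Add that a non-significant primary result whose 95% confidence interval includes a 1-point benefit will be reported as inconclusive, not as absence of a clinically relevant effect. The interval is already promised; only the rule for reading it is new.

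The cost is a less favourable power statement and a few sentences of text. No extra patients are needed and the analysis does not change.

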### 2.8 Statistical Analysis Plan

We describe the analysis for the primary objective below using the intention-to-treat (ITT) principle. We will also perform a per-protocol sensitivity analysis among treatment and assessment completers, but study conclusions will be based upon the ITT analysis results.

#### 2.8.1 Populations for Analyses

All randomized patients will have a baseline pain assessment, and those with at least one post-baseline BPI assessment on or before Day 7 will be included in the analysis of the primary objective using the modified ITT principle (i.e. participants will be analyzed according to the treatment group to which they will be randomly allocated regardless of treatment adherence status). Secondary outcome such as insomnia, anxiety, depression, fatigue, and quality of life are measured at baseline, Day 7, and Day 14. The analysis population for these endpoints will include patients who complete the baseline and one or both of the Day 7 and Day 14 assessments. Pressure pain threshold is measured at baseline before patch application, baseline 45 min after patch application and Day 7. The analysis population for this endpoint will include patients who complete the test at baseline before patch application and one or both of the other two timepoints. Additionally, all patients who apply at least 1 of the study plasters will be included in the analysis of safety.

#### 2.8.2 Analysis Plan for Primary Objective

We will plot the outcome measure trajectories by randomization arm over time and summarize each outcome measure at each assessment time by treatment arm using descriptive statistics. We expect patients’ pain levels to decrease upon first application of the PRP and then stay at a similarly decreased level with continued use over the study period. Accordingly, we will test for differences between the two study arms in post-Baseline BPI severity using a linear mixed model (LMM) predicting post-Baseline BPI severity as a function of treatment arm, controlling for Baseline BPI severity, assessment time, and randomization strata (baseline opioid use, yes/no). The test of differences between randomization arms with respect to the outcome will be based on the coefficient for treatment arm in this LMM. For our test of differences between the arms in the primary endpoint (Day 2–7 BPI severity), the LMM will have BPI severity assessments through Day 7. We will fit a similar model with BPI assessments through Day 14, but the Day 7 model will be our primary test of efficacy.

To enhance patient-centered data interpretation and decision-making, we will also perform responder analyses by considering those who experienced 30% or greater reduction in BPI severity as responders at the primary end point/Day 7 and at the end of treatment/Day 14.(Farrar et al., 2000; Farrar et al., 2001; Farrar et al., 2010). We will compare the proportion of responders in PRP and placebo plaster groups at both time points using descriptive cross-tabulations and logistic regression adjusting for the baseline outcomes and randomization strata.

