## 2 Methods and Analysis

### 2.1 Study Design

This is a prospective, single-center, two-arm, randomized, placebo-controlled trial comparing Tibetree PRP with a placebo control plaster for pain relief in cancer survivors. We plan to enroll 66 eligible patients who completed active cancer treatment and have no evidence of disease, with moderate-to-severe musculoskeletal pain for at least 3 months, from the Memorial Sloan Kettering (MSK). We use a central randomization system to allocate the participants to the experimental or control group in a 1:1 ratio. In the experimental group, patients will be instructed by a study physician/investigator to topically administrate PRP at the worst pain area daily for 14 days. In the control group, patients will be instructed by the same clinician to use the placebo patch at the same frequency for the same time course. The placebo patch mimics the color, smell, dose form, and package of the true patch. The primary outcome is pain severity measured by the brief pain inventory (BPI) at days 2–7. Secondary outcomes include pain severity measured at other time points, pain interference, fatigue, insomnia, anxiety and depression, global impression of change, treatment expectancy, and pressure pain threshold (Table 2).

**TABLE 2 T2:** Study Schedule

TIMEPOINT		Study Period														
	Enroll	Post-allocation													Close-out
	D0	D1	D2	D3	D4	D5	D6	D7	D8	D9	D10	D11	D12	D13	D14
ENROLMENT															
Eligibility screen	X														
Informed consent	X														
Allocation	X														
INTERVENTIONS															
True Patch															
Placebo Patch															
ASSESSMENTS															
Brief Pain Inventory ^1^															
Demographics and clinical		X													
Pain History	X														
Brief Fatigue Inventory		X						X							X
Hospital Anxiety and Depression Scale		X						X							X
PROMIS-10 Global Health		X						X							X
Patients’ Global Impression of Change			X					X							X
Study Allocation Belief															X
MAO Expectancy of Treatment Effects and of Side Effects of Treatment		X													
Pressure Pain Threshold test ^2^		X													X
Self-reported adherence questionnaire ^1^															
Pain Medication Diary															

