#### 2.6.2 Secondary Outcomes

• Pain severity and interference measured by the BPI at day 14.• Patients’ Global Impression of Change (PGIC) is a one item survey that will be used to define a clinically important change in pain from the patient’s perspective (Sloan et al., 2002). Patients will be asked “Compared to when the study began, how would you describe your pain now? I am: very much worse, much worse, a little worse, the same, a little improved, much improved, very much improved.” The PGIC can be used as an anchor to derive anchor-based minimally important differences (MIDs) for pain measures like the BPI.• Brief Fatigue Inventory (BFI) will be used to determine the effect of treatments on fatigue. This 9-item instrument was designed to assess one construct of fatigue severity in cancer and non-cancer populations. Three items ask patients to rate the severity of their fatigue at its “worst,” “usual,” and “now” during normal waking hours, with 0 being “no fatigue” and 10 being “fatigue as bad as you can imagine.” Six items assess the amount that fatigue has interfered with different aspects of the patient’s life during the past 24 h. The interference items are measured on a 0–10 scale, with 0 being “does not interfere” and 10 being “completely interferes” (Sloan et al., 2002). A composite fatigue severity score can be found by averaging the nine item scores. The score of the scale was found to be reliable and valid in multiple languages and diverse populations (Sloan et al., 2002; Lin et al., 2006).• Insomnia Severity Index (ISI) will be used to measure subjective insomnia severity. The ISI has seven items rated on a 5-point Likert response scale (e.g., 0 = no problem; 4 = very severe problem), yielding a total score ranging from 0 to 28 with higher scores representing more severe insomnia symptoms. The usual recall period is the “last month”; however, we will use a modified recall period of “the past week” to match our assessment schedule. The ISI authors suggest the following guidelines for interpreting the ISI total score: < 8, no clinically significant insomnia; 8-14, subthreshold insomnia; 15-21, clinical insomnia (moderate severity); >21, clinical insomnia (severe).(Bastien et al., 2001). The ISI has demonstrated internal consistency, reliability, construct validity, specificity and sensitivity in a representative sample of 1670 cancer patients.(Savard et al., 2005). The ISI has established minimally important change values to ensure that the change is not only statistically, but also clinically, meaningful to patients.(Morin et al., 2011). A reduction of eight points has been deemed to be clinically significant improvement. (Morin et al., 2011).• Hospital Anxiety and Depression Scale (HADS) will be used to explore the effect of treatments on psychological distress. HADS is a 14-item scale with seven items measuring depression and seven items measuring anxiety. Each item is answered by the patient on a four-point (0–3) response category so possible scores range from 0-21 for anxiety and depression, with higher scores indicating higher symptomatology. Established cutoffs are: 0–7 not significant; 8–10 subclinical; and 11–21 clinically significant depression/anxiety.(Zigmond and Snaith 1983). Factor analysis showed two distinct but correlated factors of anxiety and depression.(Moorey et al., 1991). The scale scores have been shown to be both reliable and valid.(Smith et al., 2002).• Patient Reported Outcomes Measurement Information System (PROMIS®) Scale v1.2 - Global Health is a brief instrument composed of 10 items that demonstrates adequate reliability and validity (Hays et al., 2009; Revicki et al., 2009) as a measure of health related QOL in general and clinical populations.(Rothrock et al., 2010; Barile et al., 2013). Patients are asked to respond to questions 1-8 and 10 on a scale of 1–5. Question nine is on a 0–10 scale (average pain rating). The measure yields two scores, Physical Health and Mental Health, that will be used as secondary outcomes to evaluate the effect of Tibetree PRP on QOL.(Hays et al., 2009). These scores will be calculated using item-level calibrations based on item response theory (IRT) scaling and then transformed to T-Scores, which are standardized such that 50 represents the mean for the US general population, and the standard deviation around that mean is 10 points.(Hays et al., 2009). Higher scores indicate better Physical and Mental Health.• MAO Expectancy of Treatment Effects (METE) has four items originally developed as the Acupuncture Expectancy Scale (AES) by Mao et al.(Mao et al., 2007) It has demonstrated reliability (Cronbach’s α of 0.82) and validity and is positively correlated with patient self-reported efficacy and satisfaction.(Mao et al., 2007). The score ranges from 4 to 20, with higher scores indicating greater expectancy.• Mao Expectancy of Side Effects of Treatment (MESET) measures the expectations of side effects and therapeutic effects of the study intervention.(Mao et al., 2014). The score ranges from 4 to 20, with higher scores indicating greater expectancy for side effects. We will use the METE and MESET to explore whether expectancy predicts treatment outcomes and may impact the observed differences between groups.• Pressure Pain Threshold: This is a study measure that a study investigator will administer. Pressure algometry is a reliable measure of pressure pain threshold. Two types of algometers will be used in this trial:(1) the FPX Wagner algometer: We will use a digital pressure algometer, FPX (Wagner instrument, Greenwich, United States), to apply pressure at the site of pain (the tender points of tissue where the patient experiences the worst pain) and two pain-neutral areas (thumbnail bed and trapezius) to derive the pressure pain threshold (the first pressure that is perceived as painful) shown to be predictive of analgesic effects (Harte et al., 2013a; Wasserman et al., 2015). The clinical researcher will apply pressure at a 0.5 kgf/cm^2^/sec increment at the tissue located at or surrounding the tested site with the tip of the algometer. The test will be terminated when participants reach their pain threshold or a pressure of 10 kgf/cm^2^. The test will be repeated three times per site, and we will take the mean threshold for analysis, measured as kgf/cm^2^. The test will be conducted three times during the study: before patch application at baseline; 45 min after patch application at baseline and at the primary endpoint (Day 7).(2) the MAST system: We will use the MAST System (Arbor Medical Innovations, Ann Arbor, MI) (Harte et al., 2013b; Schrepf et al., 2015; Wasserman et al., 2015; Treister et al., 2018; Harte et al., 2019) to apply computer-controlled pressure at the thumbnail bed to derive the PPT as well as suprathreshold measures of pain sensitivity (e.g., pain tolerance) shown to be predictive of analgesic effects.(Harte et al., 2013a; Wasserman et al., 2015). The system delivers ascending and random patterns of discrete pressures (5 s duration; 4 kgf/cm^2^/s ramp rate) at 20 s intervals, beginning at 0.25 kgf/cm^2^ and increasing in 0.25–0.50 kgf/cm^2^ steps. Pain intensity will be rated after each stimulus on a 0–100 Numerical Rating Scale. The test will be terminated when participants reach their tolerance or 10 kgf/cm^2^. PPT test with the MAST system will be conducted once before patch application at baseline only. The validity of testing pressure pain threshold with the MAST system has been demonstrated extensively (Petzke et al., 2001; Gracely et al., 2002; Giesecke et al., 2003; Petzke et al., 2003; Petzke et al., 2005; Harris et al., 2006; Geisser et al., 2008; Harris et al., 2008; Harris et al., 2009; As-Sanie et al., 2013; Henry et al., 2014; Clauw 2015). We will use this measure to explore whether pressure pain threshold predicts treatment outcomes and impacts the observed differences between groups. We will also incorporate the pressure pain threshold into the clinical outcomes to provide more objective, less biased quantification of pain and more accurate assessment of the analgesic effect of the herbal patches.• Study Allocation Belief: This is a patient-reported outcome that asks patient to guess which treatment they have received during the study to assess the adequacy of blinding.• Pain Medication Diary: Name of pain medication, the dosage/strength, number of days patients took the medication and how many pills were taken were collected in the Pain Medication Diary. A pain medication usage score was calculated according to the method developed by Robinson-Papp et al. (Robinson-Papp et al., 2015).• Adverse events: We will document all related adverse events and report any related serious adverse event promptly to IRB.

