#### 2.8.3 Analysis Plan for Secondary Objectives

The number and percent of adverse events within each treatment arm will be reported by grade. We will compare changes between the arms in insomnia, anxiety, depression, fatigue, quality of life, and pain medication usage scores using linear regressions predicting these endpoint scores at Day 7 and Day 14 (separate models) as a function of treatment arm, controlling for baseline score and randomization strata. This is equivalent to an ANCOVA model. The same analysis will be performed for PPT for the baseline (45 min after patch application) and Day 7 assessments, controlling for the pre-patch baseline assessment. We will summarize responses to the PGIC at days 2, 7, and 14 using frequencies and percentages by arm, and test for differences between arms using chi-square tests. To obtain estimates of the correlation of treatment expectancy and treatment response, we will fit a LMM similar to that specified for the primary objective, but with the addition of METE score and the interaction between treatment arm and METE score. To evaluate whether PPT predicts treatment response, we will fit a LMM similar to that specified for the primary objective, but with the addition of baseline (pre-patch) PPT score and the interaction between treatment arm and PPT baseline (pre-patch) score. Pain response variations in associated with other variables, such as sex, race/ethnicity, or age, may be addressed in post hoc analyses.

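### BPI pain severity at Day 14 is a named secondary outcome, but the stated through-Day-14 model tests an effect averaged over Days 2–14, and no adjusted Day 14 mean difference is specified

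*Protocol article*

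**What the plan says.** Section 2.6.2 (Secondary Outcomes) opens its list with "Pain severity and interference measured by the BPI at day 14". Section 2.1 words the same item more loosely: "Secondary outcomes include pain severity measured at other time points, pain interference, fatigue, insomnia, anxiety and depression".

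Section 2.8.2 gives a linear mixed model for post-baseline BPI severity with treatment arm as predictor, "controlling for Baseline BPI severity, assessment time, and randomization strata (baseline opioid use, yes/no"). No arm-by-time term is named. On the test it says: "The test of differences between randomization arms with respect to the outcome will be based on the coefficient for treatment arm in this LMM". The reason offered is that pain under the plaster should fall at first application and "then stay at a similarly decreased level with continued use over the study period". The extension to the second week is one sentence: "We will fit a similar model with BPI assessments through Day 14, but the Day 7 model will be our primary test of efficacy".

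Section 2.8.2 also plans trajectory plots and descriptive summaries by arm at every assessment. It adds a responder comparison (at least a 30% reduction in BPI severity) at Day 7 and Day 14 by adjusted logistic regression.

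Section 2.8.3 plans "linear regressions predicting these endpoint scores at Day 7 and Day 14 (separate models") for insomnia, anxiety, depression, fatigue, quality of life and pain medication use. BPI severity is not in that list.

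**The concern.** The outcome is a score at one day, whereas the stated analysis yields one number pooled over all post-baseline days. The two agree only if the difference between arms is the same on every day from Day 2 to Day 14, which the model imposes and cannot check.

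The data through Day 14 include all the days of the primary endpoint. A positive result from this model could therefore come largely from the first week and still be read as the Day 14 result. Section 1 states a two-week treatment, and section 3 intends the data to help design a longer trial, so a Day 14 figure that is really an average would be carried forward with the wrong meaning. The lesser symptom scales do get an adjusted Day 14 comparison, while mean pain severity does not.

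**Working it through.** **The plan's own figure.** Section 2.7 gives a detectable standardised difference of 0.74 with 30 per arm, two-sided alpha 0.05 and power 0.80. A two-sample t calculation gives 0.736, with power 0.805 at 0.74, so the figure is reproduced. At the stated SD of 2 to 3, 0.74 × 2 = 1.48 and 0.74 × 3 = 2.22 points. The illustrations below use 1.5 points, the lower end of that range.

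**Inputs.** Severity is asked daily (key to Table 2), so Days 2–14 give 13 post-baseline assessments, of which Days 2–7 are 6. The article gives no correlation structure. Two are assumed here, both with complete data: compound symmetry with correlation 0.7, and AR(1) with correlation 0.8.

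**What the coefficient estimates.** With one arm effect and correlation matrix R, the coefficient is the sum of (weight × daily arm difference), with weights R⁻¹1 / (1′R⁻¹1).

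- Compound symmetry gives equal weights of 1/13 = 0.077. Day 14 carries 7.7% and Days 2–7 carry 6/13 = 46%.
- AR(1) gives each end day 1/(13 − 11 × 0.8) = 1/4.2 = 0.238 and each interior day 0.2/4.2 = 0.048. Day 14 carries 24% and Days 2–7 carry (1 + 5 × 0.2)/4.2 = 48%.

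**Assumed patterns of the arm difference (BPI points).**

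| Pattern | Pooled, compound symmetry | Pooled, AR(1) | True Day 14 |
|---|---|---|---|
| Constant 1.5 | 1.50 | 1.50 | 1.5 |
| 1.5 to Day 7, then 0 | 0.69 | 0.71 | 0 |
| 1.5 to Day 7, then linear to 0 at Day 14 | 1.04 | 0.93 | 0 |
| 1.5 to Day 7, then 0.5 | 0.96 | 0.98 | 0.5 |
| Linear from 0 at Day 2 to 1.5 at Day 14 | 0.75 | 0.75 | 1.5 |

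Sample arithmetic under equal weights:

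- Row 2: 1.5 × 6/13 = 0.69.
- Row 3: Days 8–14 contribute 1.5 × (6+5+4+3+2+1+0)/7 = 4.5, so (9 + 4.5)/13 = 1.04.
- Row 4: (6 × 1.5 + 7 × 0.5)/13 = 0.96.

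In the non-constant rows the gap from the Day 14 value runs from 0.46 (0.96 − 0.5) to 1.04.

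**Precision given up by a Day 14 contrast.** Relative to a single day, the variance of the pooled estimate is (1 + 12 × 0.7)/13 = 0.723 under compound symmetry and (1 + 0.8)/4.2 = 0.429 under AR(1). The Day 14 standard error is therefore 1/√0.723 = 1.18 to 1/√0.429 = 1.53 times as large.

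**The case against.** The strongest reply is that the single coefficient is a reasoned choice. Section 2.8.2 expects relief to appear at once and hold, and under a constant difference the pooled coefficient is the Day 14 effect, as the first row of the table shows. That stands as arithmetic. However, the sentence describes pain under the plaster. The difference between arms also depends on how the placebo arm moves, and the stated model offers no check.

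Second, the wording in section 2.1 suits an all-days model, and an analysis plan not shown may define a Day 14 contrast. This makes the point smaller. But the article does state both a Day 14 outcome and a test coefficient, and the two do not match. The ANCOVA mentioned in section 2.7 is illustrated at Day 7 and does not settle Day 14 pain.

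Some stronger readings are not supported:

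- A reader might infer that Day 14 severity is never estimated, or that the plan cannot show whether relief lasts. The plots, the daily summaries by arm and the adjusted Day 14 responder comparison would reveal a marked loss of effect. What is missing is the adjusted mean difference, the scale on which section 2.7 calls 1 point clinically important.
- A reader might treat persistence in the second week as the leading secondary question. The article ranks no secondary outcome, and its stated aim is immediate or temporary relief.
- A reader might see a conflict between separate Day 7 and Day 14 regressions and a population of patients who "complete the baseline and one or both of the Day 7 and Day 14 assessments". There is none, because a patient with one follow-up enters the regression for that day. Under assumed outcome-related dropout of 8.5% after Day 7, a simulation gave −0.47 for the separate Day 14 regression against a true −0.50, a difference of 0.03 SD. Preferring a joint model there is a matter of taste.

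**Conclusion.** The point holds in a limited form. As written, the through-Day-14 model gives a weighted average effect over Days 2–14, and no adjusted Day 14 mean difference in BPI severity is specified, although that is a named secondary outcome. If the effect is constant, nothing is lost. Under the assumed non-constant patterns the pooled coefficient misses the Day 14 difference by about 0.5 to 1 point, in either direction.

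The effect patterns and both correlation structures are assumptions. The weight on Day 14 is sensitive to the correlation (8% or 24%), but the share of Days 2–7 is nearly half under both. The primary Day 2–7 test and the sample size are not affected. This is an inexpensive improvement to a secondary analysis and no threat to the trial's main conclusion.

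**What to change.** In section 2.8.2, add an arm-by-time term to the through-Day-14 model, with day as a factor, and report the Day 14 contrast with its 95% confidence interval as the secondary outcome. Alternatively, add BPI severity to the endpoints given a Day 14 regression in section 2.8.3. Keep the pooled Days 2–14 average as supporting description, and leave the primary Day 2–7 model as it is.

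The cost is a change of wording, since the daily scores are already collected. The Day 14 contrast will be less precise than the pooled average, with a standard error about 1.2 to 1.5 times as large under the correlations assumed above.
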